### Study population

The study population consists of adult patients with CTEPH who are treated with riociguat monotherapy and have completed their final BPA session 6 months prior to screening. Patients are recruited from routine follow-up visits at the participating centres.

Eligible patients must have demonstrated an mPAP <30 mmHg on right heart catheterisation (RHC) performed within 3 months prior to inclusion. If no recent RHC is available, it will be performed after informed consent. Patients with an mPAP ≥30 mmHg are excluded.

Inclusion criteria include: age ≥18 years; diagnosis of CTEPH according to prevailing European guidelines; treatment with riociguat monotherapy initiated prior to or within 2 weeks after the first BPA session; availability of a documented post-BPA follow-up RHC performed within the last 3 months or an anticipated post-BPA follow-up RHC with an mPAP <30 mmHg as determined by the treating physician’s judgement; ability to comply with study procedures; and provision of written informed consent.

Exclusion criteria include: WHO functional class IV; cardiac index <2.2 L/min/m²; prior PEA; post-BPA follow-up RHC within 3 months indicating an mPAP ≥30 mmHg; participation in another interventional drug trial; severe comorbidities limiting life expectancy to less than 1 year; or any condition that, in the investigator’s judgement, precludes safe participation.

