### Randomisation and allocation

After confirmation of eligibility and completion of baseline assessments, participants are randomised in a 1:1 ratio to either discontinuation or continuation of riociguat. Randomisation is performed in CastorEDC (Ciwit B.V., Amsterdam, The Netherlands) using block randomisation with variable block sizes. Stratification is applied by riociguat dose at inclusion (daily dose of <6 mg vs ≥6 mg) and time since last BPA, distinguishing incident patients (scheduled for RHC as part of standard clinical follow-up) from prevalent patients (those in long-term follow-up, screened by transthoracic echocardiography (TTE); last RHC performed more than 3 months ago). Due to the nature of the intervention, the trial is conducted as an open-label study. Blinding was considered impractical given the recognisable side effects of riociguat and the objective nature of the majority of primary and key secondary outcomes. However, all physicians performing outcome measurements will be blinded to treatment allocation.

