**Figure 2 F2:**
[figure not shown]
Outline of study protocol. At the end of study follow-up, participants will also complete a survey assessing satisfaction with the discontinuation strategy. 6MWD, 6-min walking distance; CPET, cardiopulmonary exercise testing; FC, functional class; QoL, quality of life; RHC, right heart catheterisation; TTE, transthoracic echocardiogram.

A predefined safety evaluation is performed at week 8 (±3 weeks). Clinical worsening is defined as the simultaneous occurrence of all three of the following criteria: (1) >15% decrease in 6MWD, (2) progression to WHO functional class III/IV, and (3) increase in NT-proBNP of ≥30% to a level of ≥300 pg/mL. This definition is adapted from prior pulmonary arterial hypertension (PAH) and CTEPH trials and aligns with criteria used in the STELLAR trial.^3
15–18^ If clinical worsening is confirmed, TTE is performed and riociguat is reinitiated in the discontinuation group. Unscheduled evaluations may be performed at the investigator’s discretion in case of suspected clinical deterioration.

At study completion, participants complete a survey assessing satisfaction with the discontinuation strategy. Riociguat may be reintroduced after the end-of-study RHC at the discretion of the treating physician and patient.

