### Sample size calculation

The sample size calculation was performed for the primary endpoint, mPAP at 16 weeks, and for the two secondary endpoints highest in the hierarchy (NT-proBNP and 6MWD). Sample size calculations were performed using the formula: n=f(α,β)×2×σ²/d², where f(α,β) = (Φ⁻¹(α) + Φ⁻¹(β))². For the primary endpoint (mPAP at 16 weeks), assuming a one-sided α of 0.025, power of 90%, SD of 4.9 mmHg and an NI margin of 4 mmHg, 64 participants (32 per group) are required. Allowing for a 10% dropout rate, the target sample size for the primary endpoint is 70 participants.

For NT-proBNP, a NI margin of 30% was chosen, reflecting a clinically meaningful change commonly used in PH and heart failure trials.^20–24^ NT-proBNP values from preliminary data were log-transformed (mean 5.04, SD 1.15), corresponding to a NI margin of 1.51 on the log scale. This yielded a required sample size of 26 participants (13 per group) with 90% power and one-sided α=0.025; accounting for dropout, 29 participants are required. For 6MWD, a NI margin of 15% was used, consistent with widely used definitions of clinical worsening in PAH and CTEPH trials. Using a mean of 467 m and an SD of 95 m of riociguat-treated post-BPA patients derived from a study by Wiedenroth *et al*,^25^ 66 participants (33 per group) are required with 85% power and one-sided α=0.025. After allowing for 10% dropout, 74 participants are required. As the largest sample size was required for 6MWD, the total sample size was set at 74 participants.

NT-proBNP was prioritised in the hierarchical testing strategy because it is an objective biomarker that reflects haemodynamic status. Also, the planned sample size provides greater statistical power for NT-proBNP than for 6MWD.

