### Statistical analysis

All analyses will be performed using R (R Foundation for Statistical Computing, Vienna, Austria). Continuous variables will be summarised as mean±SD or median (IQR) as appropriate; categorical variables as counts and percentages. Normality will be assessed using histograms and Q–Q plots. Skewed variables will be log-transformed when necessary.

The null hypothesis is that riociguat discontinuation is inferior to continuation. NI will be concluded if the upper bound of the two-sided 95% CI for the baseline-adjusted between-group difference does not exceed the predefined NI margin. A one-sided significance level of α=0.025 will be used.

A secondary analysis of the primary endpoint (mPAP at 16 weeks) will include an analysis of covariance (ANCOVA), with baseline mPAP as a covariate. Treatment group will be included as the main effect, with riociguat dose and incident/prevalent status included as fixed factors to account for stratification at randomisation. To control the type I error rate, hierarchical testing will be applied. Secondary continuous outcomes will be analysed using ANCOVA or linear regression adjusted for baseline values. Binary outcomes will be analysed using χ^2^ or Fisher’s exact tests. Ordinal outcomes will be analysed using stratified Wilcoxon tests or linear mixed models for repeated measures, as appropriate. All estimates will be reported with two-sided 95% CIs.

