### Health economic evaluation

A prospective economic evaluation will be conducted after completion of the trial. Costs related to medication use, healthcare consumption (including outpatient visits, hospital admissions and emergency department visits) and patient travel will be collected prospectively. Health-related quality of life will be assessed using the EuroQol five-dimensional five-level questionnaire (EQ-5D-5L) and Living with Pulmonary Hypertension Questionnaire (LPHQ). These outcomes will be incorporated into a formal health-economic evaluation to estimate cost-effectiveness in terms of quality-adjusted life years. Secondary endpoints for the secondary study objectives are outlined in table 2.

**Table 2 T2:** Secondary endpoints for the secondary objectives

Secondary objectives	Endpoints for secondary objectives
To assess the societal impact benefits associated with riociguat discontinuation in CTEPH patients with mPAP <30 mmHg post-BPA	Economic outcomes Between-group difference in costs related to PH medication Between-group difference in healthcare consumption Frequency of visits to expert centres versus local hospitals Travel distance for medical care Number of emergency department visits Patient-related outcomes Between-group difference at 16 weeks in the following parameters: WHO functional class Quality of life questionnaire scores LPHQ EQ-5D-5L Number of predefined graded adverse events: Mean gradation of hypotension Mean gradation of dizziness Mean gradation of diarrhoea

BPA, balloon angioplasty; CTEPH, chronic thrombo-embolic pulmonary hypertension; EQ-5D-5L, EuroQol five-dimensional five-level questionnaire ; LPHQ, Living with PH questionnaire; mPAP, mean pulmonary artery pressure; PH, pulmonary hypertension.

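### No baseline adjustment is stated for ordinal outcomes; if week-16 WHO functional class is compared by a Wilcoxon test stratified only by the randomisation factors, power is given up that baseline class would recover

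*Protocol article*

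**What the plan says.** All references are to the protocol article.

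- **Method.** The Statistical analysis section covers ordinal outcomes in one sentence: "Ordinal outcomes will be analysed using stratified Wilcoxon tests or linear mixed models for repeated measures, as appropriate". It names neither the strata nor the outcomes to which each method applies.
- **Contrast.** Shortly before, the same paragraph says: "Secondary continuous outcomes will be analysed using ANCOVA or linear regression adjusted for baseline values". Nothing equivalent is said for ordinal outcomes.
- **Endpoint.** Table 2, under Health economic evaluation, lists "Between-group difference at 16 weeks in the following parameters: WHO functional class" among the patient-related outcomes of the secondary objective.
- **Strata.** The only ones described are in Randomisation and allocation: "Stratification is applied by riociguat dose at inclusion (daily dose of <6 mg vs ≥6 mg) and time since last BPA", the latter split into incident and prevalent patients.
- **Baseline class.** It has to be recorded. Study population has "Exclusion criteria include: WHO functional class IV", and the clinical worsening definition in Follow-up and safety monitoring includes "progression to WHO functional class III/IV", which cannot be judged without a starting class.

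**The concern.** A patient's functional class at week 16 is likely to depend on the class at entry. A comparison that does not use the entry class carries that between-patient variation as noise. The article removes this noise for continuous outcomes and does not say that it will for ordinal ones. On the natural reading, a stratified Wilcoxon test uses the strata that the article describes, and baseline class is not among them.

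At stake is how well the trial can detect a shift in functional class after stopping, with about 37 patients per arm. Because baseline class is collected anyway, any power lost is lost for no saving.

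The other option, a linear mixed model, raises a different and smaller question. It scores the classes as equally spaced numbers and yields a difference in mean class, which is harder to read clinically than an odds ratio.

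**Working it through.** **The plan's own figure.** The article states that "the total sample size was set at 74 participants", driven by 6-minute walk distance. With SD 95 m, margin 0.15 × 467 = 70.05 m, 85% power and one-sided α of 0.025:

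n per group = 2 × (1.960 + 1.036)² × 95² / 70.05² = 33.03.

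Taken as 33 per group this is 66, and 66 / 0.9 = 73.3, so 74. The figure reproduces. No power or effect size is stated for WHO class.

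**Inputs from the article.** N = 74; "participants are randomised in a 1:1 ratio to either discontinuation or continuation of riociguat", so 37 per arm; two-sided 5% level (one-sided 0.025); class IV excluded at entry.

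**Inputs assumed, not in the article.** Baseline class mix I/II/III of 35/55/10%; treatment effect of 1.8 on the log-odds scale, conditional on the patient; a range of correlations between baseline and week-16 class.

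**Model.** Each patient has an effect u ~ N(0, s²). Baseline class is u plus a logistic error, cut into three classes at the assumed mix. Week-16 class is u + 1.8 × (discontinuation) plus a new logistic error, cut at the same points. Setting s to about 0, 1.5, 2.5 and 4 gives observed correlations of about 0, 0.3, 0.5 and 0.65. Each setting has 800 to 1,000 simulated trials.

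**Analyses compared.**
- A: van Elteren (stratified Wilcoxon) test with four strata unrelated to outcome, standing for the two randomisation factors.
- B: van Elteren test stratified by baseline class.
- C: linear model on the class number with baseline as covariate, standing for a mixed model that uses baseline.
- D: proportional-odds model with baseline class, likelihood-ratio test.

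**Power (%) at N = 74**

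| Correlation | A | B | C | D | D − A |
|---|---|---|---|---|---|
| 0 | 95 | 96 | 96 | 97 | 2 |
| 0.3 | 81 | 86 | 87 | 87 | 6 |
| 0.5 | 55 | 72 | 73 | 74 | 19 |
| 0.65 | 32 | 52 | 54 | 56 | 24 |

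Compare within rows only. The conditional effect is held fixed while patient heterogeneity grows, so the marginal effect, and with it all power, falls down the table. The simulation standard error of a single power is at most √(0.25/800) = 1.8 points, so the 2-point gap in the first row is about the size of simulation noise.

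**Reading across.** B falls short of D by 1 to 4 points and C by 0 to 2. The loss therefore comes from leaving out baseline class, not from ranks or from equal spacing.

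**Type I error.** With no effect, at correlations of about 0, 0.3 and 0.5, all four analyses rejected in 4 to 6% of trials. The null case was not run at 0.65.

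**Sensitivity.** With 66 evaluable patients, the number before the dropout allowance, D − A is about 1, 7, 20 and 21 points down the same rows. With a smaller effect of 1.2 at N = 74, it is about 2 points at correlation 0 and 7.5 at 0.3.

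**Analytic check.** Baseline adjustment multiplies the residual variance by about 1 − r². So 74 patients analysed with adjustment match 74 / 0.91 = 81 without it at r = 0.3, 74 / 0.75 = 99 at r = 0.5 and 74 / 0.51 = 145 at r = 0.7.

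**The case against.** The strongest reply is that the article never says baseline class is left out. The strata of the Wilcoxon test are unnamed, the randomisation factors are tied by name only to the mPAP analysis of covariance, and a Wilcoxon test stratified by baseline class would satisfy the sentence as written. The article is a condensation, and a separate analysis plan may settle the matter. This stands as a limit: the power loss is conditional on the strata being the randomisation factors. It does not remove the point. The article makes a positive statement of method, mentions baseline for continuous outcomes and not for ordinal ones, and describes no strata that include class.

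Several stronger readings are tempting, and the documents do not support them:

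- **Both options lose power.** They do not. A repeated-measures model can use baseline, and a linear model that does so comes within 0 to 2 points of the ordinal model. The objection to it is interpretation alone.
- **A Wilcoxon test gives no estimate, so the promise of confidence intervals fails.** A rank comparison has an effect measure, the Mann-Whitney probability with ties handled, and an interval can be given for it.
- **WHO class is the main clinical outcome, and a missed shift would be taken as proof of safety.** WHO class is a Table 2 item, outside the non-inferiority hierarchy and the sample size calculation. The safety endpoints are in Table 1, and class progression already enters through clinical worsening. Nothing in the article treats a non-significant class comparison as evidence of safety.
- **The linear mixed model should go for every ordinal outcome.** Table 2 also lists mean gradings of hypotension, dizziness and diarrhoea. There the endpoint is itself a mean, and a linear model can fit it.

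**Conclusion.** The point holds as a minor improvement. No baseline adjustment is stated for ordinal outcomes, and the strata that are described omit baseline WHO class. If the week-16 comparison is a Wilcoxon test on those strata alone, the cost against a baseline-adjusted ordinal model is negligible at correlation 0 (about 2 points), small at 0.3 (about 6), and substantial at 0.5 and 0.65 (about 19 and 24).

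These sizes rest on an assumed class mix and effect, on randomisation strata unrelated to class, and on a correlation that the article does not give. If dose or incident/prevalent status predicts class, the loss would be smaller. The direction does not depend on the exact values once class at entry predicts class at week 16. The primary non-inferiority conclusion is unaffected.

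**What to change.** For WHO functional class only, name one analysis before outcome data are seen. Either of these serves:

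- a proportional-odds model for week-16 class with treatment, baseline class and the two stratification factors, reporting a common odds ratio with 95% CI; or
- a Wilcoxon test stratified by baseline class. Crossing three baseline classes with the four randomisation cells would make 12 strata for 74 patients, about 6 each, so baseline class alone is the practical choice.

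The linear mixed model can stay for other graded outcomes where a mean is the stated endpoint.

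The cost is a change of wording, with no new data and no change to sample size. The small downside of the first option is the proportional-odds assumption, which can be checked against the rank test stratified by baseline class.

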### Analysis set

The primary analysis will be conducted in the per-protocol population, as an intention-to-treat (ITT) analysis can be considered anticonservative in a NI study testing discontinuation. Participants who restart riociguat due to clinical worsening will be analysed in the continuation group. As a secondary analysis, we will perform an ITT analysis according to randomised allocation, reflecting the clinical discontinuation strategy including re-initiation and testing the safety of the stopping strategy. In addition, two exploratory analyses will be performed: a modified ITT analysis excluding participants who restarted riociguat from the discontinuation group to explore outcomes among patients who tolerate treatment withdrawal without re-initiation, and a subgroup analysis comparing participants who restarted riociguat with the continuation group to assess haemodynamic response following re-initiation. Non-compliant patients who meet protocol violations will be excluded as part of the modified per-protocol (PP) analysis. Missing data will not be imputed. However, participants who withdraw before the week 8 clinical worsening assessment because of clinical deterioration, or for whom the reason for withdrawal is unknown, will be conservatively classified as having experienced clinical worsening.

To account for potential loss of participants from the primary per-protocol analysis due to clinical worsening, predefined scenarios were incorporated into the statistical analysis planning. Based on power simulations, the study is expected to retain approximately 80% power if up to 35% of participants are lost from the intervention group. To mitigate the risk of insufficient power, the randomisation ratio will be reassessed after inclusion of 50% of the planned sample size. If ≥30% or ≥40% of participants in the discontinuation group have restarted riociguat at that point, the randomisation ratio will be adaptively adjusted from 1:1 to 2:1 or 3:1, respectively, in favour of the discontinuation group. If ≥50% of participants in the discontinuation group experience clinical worsening, the study will be terminated for safety reasons, as such a rate is considered clinically unacceptable.

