**Figure 1 F1:**
[figure not shown]
mPAP before, during and after BPA in patients treated with riociguat (red, n=21) and in patients without PH-targeted therapy (blue, n=10). In the riociguat group, baseline measurement was obtained prior to treatment initiation. Mean (±SD) mPAP values in the riociguat group were 44.4±11.7 mmHg at baseline, 35.9±10.0 mmHg at first BPA, 29.3±6.7 mmHg at last BPA and 29.0±7.0 mmHg at follow-up. Corresponding values in the no-therapy group were 36.6±10.1 mmHg, 34.2±9.0 mmHg, 28.7±10.8 mmHg and 29.6±6.9 mmHg. BPA, balloon pulmonary angioplasty; mPAP, mean pulmonary artery pressure; PH, pulmonary hypertension.

Given the absence of prospective evidence in Western populations and the lack of standardised discontinuation criteria, this randomised non-inferiority (NI) trial aims to assess the safety and feasibility of stopping riociguat after BPA in patients with mPAP <30 mmHg (primary objective), including a prospective health economic evaluation of the societal and patient-related benefits of riociguat discontinuation (secondary objective).

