### Objectives and endpoints

The primary endpoint is the between-group difference in mPAP at rest, measured by RHC at 16 weeks. Secondary endpoints for the primary study objective are outlined in table 1.

**Table 1 T1:** Secondary outcomes for the primary study objective

Objectives	Secondary endpoints
To investigate if discontinuation of riociguat is non-inferior to its continuation in CTEPH patients with mPAP <30 mmHg post-BPA	Efficacy endpoints: Between-group differences at 16 weeks for the following parameters in hierarchical order: NT-proBNP (assessed for non-inferiority) 6MWD (assessed for non-inferiority) PVR Cardiac index Between-group differences at 16 weeks in exercise capacity in post hoc analysis: CPET variables: oxygen uptake, workload, heart rate, respiratory exchange ratio, ventilation, oxygen saturation, oxygen pulse, equivalent carbon dioxide Change in modified Borg dyspnoea scale Safety endpoints: Between-group differences at 16 weeks in the following parameters: Number of adverse events and severe adverse events Proportion of participants with mPAP ≥38 mmHg at RHC Proportion of participants meeting the clinical worsening criteria at week 8 Feasibility of the strategy: Is TTE sufficient to replace RHC at the end of study follow-up? The correlation between TTE and RHC parameters Right ventricular systolic pressure Tricuspid annular plane systolic excursion Proportion of participants missed by TTE with mPAP ≥38 mmHg at 16 weeks RHC Is the discontinuation strategy feasible for implementation in clinical practice? Proportion of participants missed by the clinical worsening criteria with mPAP ≥38 mmHg at 16 weeks Participants' satisfaction with the protocol

BPA, balloon angioplasty; CPET, cardiopulmonary exercise testing; CTEPH, chronic thrombo-embolic pulmonary hypertension; mPAP, mean pulmonary artery pressure; 6MWD, 6-min walking distance; NT-proBNP, N-terminal pro-B-type natriuretic peptide; PVR, pulmonary vascular resistance; RHC, right heart catheterisation; TTE, transthoracic echocardiography; WHO, world health organisation.

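### The primary per-protocol analysis counts discontinuation patients who worsen and restart riociguat as continuation patients, which can pull the comparison towards non-inferiority

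*Protocol article*

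**What the plan says.** The Analysis set section of the protocol article opens with "The primary analysis will be conducted in the per-protocol population", on the ground that ITT may be anticonservative when discontinuation is tested for non-inferiority. The next sentence is "Participants who restart riociguat due to clinical worsening will be analysed in the continuation group".

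Under Follow-up and safety monitoring, "A predefined safety evaluation is performed at week 8 (±3 weeks"), and "If clinical worsening is confirmed, TTE is performed and riociguat is reinitiated in the discontinuation group". The endpoint comes later: "The primary endpoint is the between-group difference in mPAP at rest, measured by RHC at 16 weeks".

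ITT by randomised allocation is a secondary analysis, described as "reflecting the clinical discontinuation strategy including re-initiation and testing the safety of the stopping strategy". An analysis that drops restarters from the discontinuation arm, and a comparison of restarters with the continuation group, are exploratory. The power planning in the same section speaks of "potential loss of participants from the primary per-protocol analysis due to clinical worsening".

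**The concern.** A per-protocol analysis normally leaves out patients who depart from their assigned treatment. Here they change sides. Those moved were tapered off riociguat, met all three worsening criteria and then restarted, so they did not follow the continuation regimen. If worsening tracks mPAP, removing them lowers the discontinuation mean. If their mPAP is still raised at week 16, adding them raises the control mean. Both effects shrink the difference that is compared with the 4 mmHg margin, and nothing moves in the opposite direction.

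The non-inferiority conclusion for a trial that "aims to assess the safety and feasibility of stopping riociguat after BPA" rests on this analysis. The ITT analysis, which the plan itself says tests the safety of the strategy, is not required to agree.

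**Working it through.** **Plan's own figures.** The sample size section gives one-sided α 0.025, power 90%, SD 4.9 mmHg and margin 4 mmHg. The formula n = (1.960 + 1.282)² × 2 × 4.9² / 4² gives 31.5, rounded up to 32 per group. The stated 64 reproduces.

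**Power at 35% loss.** The plan says about 80%. Of 32 discontinuation patients, 32 × 0.65 = 20.8 remain.
- Excluded: 20.8 against 32 gives 82.6% (normal) or 81.1% (t).
- Moved: 20.8 against 32 + 11.2 = 43.2 gives 86.4% or 85.3%.

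Exclusion is closer, but an approximate 80% does not settle which was assumed.

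**Direction of the bias.** Assume equal arms. Let p be the share of the discontinuation arm that restarts. Let T and R be the mean week-16 mPAP excess over true continuers among non-restarters and restarters. Then:
- by randomised arm: (1 − p)T + pR
- restarters excluded: T
- restarters moved: T − R·p/(1 + p)

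Moving gives a smaller difference than excluding whenever R > 0. It gives a smaller difference than ITT when R > T(1 + p)/(2 + p), that is, above 1.10/2.10 = 52% of T at p = 0.10 and above 1.35/2.35 = 57% of T at p = 0.35. At R = 0 the moved estimate equals T and ITT is the more diluted.

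*Example (assumed p = 0.30, R = 8 mmHg, true difference by randomised arm 4 mmHg).* T = (4 − 0.3 × 8)/0.7 = 2.29. Moved: 2.29 − 8 × 0.3/1.3 = 0.44 mmHg. In simulation (33 per arm, SD 4.9) non-inferiority is declared in 68% of trials with restarters moved, 24% with them excluded and about 2.5% by randomised arm.

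**False non-inferiority against the off-drug difference.** Simulation with 33 per arm, the plan's SDs (3.43 at baseline, 3.8 for change, correlation −0.08), baseline-adjusted ANCOVA and a true off-drug difference of 4 mmHg. Assumptions not in the document are the restart rate, recovery (restarters regain all or none of the 4 mmHg by week 16) and the correlation between restart propensity and mPAP change (0 to 0.5). Results at 20% restarting:

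| Correlation | Recovery | Moved | Excluded | ITT | Excluded and ITT both required |
|---|---|---|---|---|---|
| 0 | full | 2.3% | – | 11.9% | – |
| 0.25 | full | 7.8% | – | 13.1% | – |
| 0.5 | full | 19.8% | 9.9% | 14.1% | 8.8% |
| 0.5 | none | 35.8% | 9.4% | 2.4% | 2.4% |

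Repeat runs put the 35.8% figure at up to 38%. Over correlations 0 to 0.5 and full to no recovery, the moved analysis ranges over about 3-15% at 10% restarting, 2-38% at 20% and 2-56% at 30%.

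**The case against.** The sponsor's reason for avoiding ITT is sound over part of the range. If restarters recover fully, ITT dilutes the off-drug difference. At 20% restarting and correlation 0 to 0.25, ITT declares non-inferiority in 12-13% of trials against 2-8% under the stated rule. The worsening definition contains no mPAP, so a strong correlation is not established. It needs three criteria at once, so restarts may be few: at 3-5% restarting, false non-inferiority under the rule is 2-7%. The 30% and 40% figures in the plan are adaptation triggers and not forecasts. Exclusion and ITT analyses are already planned at lower rank.

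All of this stands, and it limits the size of the problem. It does not justify the transfer, since dilution of ITT is an argument for leaving restarters out of the per-protocol set.

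Four stronger readings that a reader might infer are not supported:
- *The rule is always more anticonservative than ITT, or the 2.5% level always fails.* With full recovery and no correlation it stays near 2.5%.
- *ITT's 12-14% is an error for the strategy as randomised.* With full recovery at 20% restarting, that difference is 0.8 × 4 = 3.2 mmHg, inside the margin.
- *Safety endpoints are also reassigned.* Nothing in the document says so, and its worsening thresholds count patients in the discontinuation group.
- *The power planning proves that exclusion was intended.* The wording about loss leans that way, but the power figure does not decide it.

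**Conclusion.** The point holds in conditional form. The reassignment sentence governs the primary analysis and transfers failures of the tested strategy to the control arm. Wherever restarters' week-16 mPAP remains above that of true continuers, the estimate lies closer to non-inferiority than under exclusion. Its effect on the error rate runs from none to very large (about 2% to 38% at 20% restarting), depending on three quantities that the document does not give. A primary analysis should not rest on the favourable end of that range when a simple alternative exists. The secondary ITT analysis mitigates the problem but does not cure it, because the conclusion does not depend on it. The sentence about loss from the per-protocol analysis also needs to be reconciled with the reassignment sentence.

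**What to change.** 1. Delete the reassignment sentence. Exclude restarters from the per-protocol set, say so, and never analyse them as controls. Align the wording on loss with this.
2. Conclude non-inferiority only if both the per-protocol and the as-randomised ITT analyses meet the 4 mmHg margin.
3. Prespecify a sensitivity analysis in the randomised arms that penalises restarters' on-drug week-16 mPAP, for example by adding the 4 mmHg margin. It is needed because requiring both analyses still leaves about 9% false non-inferiority with full recovery, 20% restarting and correlation 0.5. The penalised analysis gives 2.5% there and 0.4% with no recovery. The 2.5% is partly by construction, since the penalty equals the simulated effect.
4. State that safety endpoints are reported by randomised arm.

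The cost is protocol wording, two more model fits and some power. At a true difference of 0 with 10% restarts, joint power is about 98.6% against 99.5% for the per-protocol analysis alone. At a true difference of 2 mmHg with 30% restarts and no recovery, it is about 54% against 82%. The penalised analysis would pass in only about 11% of trials in that last setting, so it suits a sensitivity role better than a decision rule.
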